Key Inclusion and Exclusion Criteria	Inclusion Criteria: (1) Hypoxemic acute respiratory failure plus evidence of active SARS CoV-2 infection (positive for SARS CoV-2 using antigen or PCR test within the 10 days prior to randomization) (2) C-reactive protein > 32 mg/dl Exclusion Criteria: (1) Prisoners (2) Women who may be pregnant, are pregnant, or who are breast feeding (3) Subjects who are unable or unwilling to give written informed consent or to comply with study protocol and who have no legal authorized representative (LAR) available to give consent on their behalf (4) Individuals with a known allergy to citicoline (5) Subjects that are taking medications that contain L‐Dopa, centrophenoxine, or meclofenoxate (6) Individuals with hypertonia of the parasympathetic nervous system (7) Subjects who, in the clinicians estimation, will be unlikely to survive the protocol duration due to imminent and unavoidable risk of death (8) Individuals being treated with extracorporeal membrane oxygenation (ECMO) (9) Individuals with multiple organ failure
Study Type	Single-site, double-blinded, placebo-controlled, and randomized Phase 1/2 dose-ranging and safety study
Date of First Enrollment	7/14/2023
Sample Size	Planned: 80 Enrolled: 15
Recruitment Status	Recruiting
Primary Outcome	A statistically significant difference in lowest recorded S_p_O_2_:F_i_O_2_ ratio on study day 3, at *P* < 0.05
Key Secondary Outcomes	Statistically significant differences (*P* < 0.05) in: (1) Lowest recorded S_p_O_2_:F_i_O_2_ value on study days 1–2 and 4–8, or until extubation (whichever comes first) (2) Lowest Sequential Organ Failure Assessment (SOFA) score on study days 1, 3, 5, and 8 (3) Highest COVID Ordinal Outcomes Scale score on study days 1, 3, 8, 15, and 29 Oxygen-free days through day 28 Ventilator-free days through day 28 ICU-free days through day 28 Hospital-free days through day 28
Ethics Review	Approved by The Ohio State University Biomedical Sciences Institutional Review Board on 3/28/23 [name] [contact]
IPD sharing statement	Plan to share IDP: Yes All data will be deposited to the Dataverse that is supported by Harvard University under waivers providing for public availability of data repository starting 12 months after the trial begins and will be deposited every six months thereafter. This repository provides metadata, persistent unique identifiers, and long-term access for at least 10 years

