#### Outcomes

The primary goals of SCARLET are to establish the safety of citicoline in hospitalized SARS CoV-2-infected patients with HARF, to generate preliminary evidence of efficacy, and to identify an optimal citicoline dose for Phase 3 efficacy trials. There are therefore both safety- and efficacy-related primary outcome measures.

A particular dose of citicoline will be considered safe if the number of SAEs attributable to that citicoline dose (in the view of treating clinicians) remains below the threshold indicative of excessive toxicity once all 20 subjects have been treated (see Table 2).

**Table 2 Tab2:** Number of patients with SAEs required to claim excessive toxicity

No. of patients	1–2	3–4	5–7	8–10	11–14	15–17	18–20
No. with SAEs	–	2	3	4	5	6	7

The primary clinical outcome is a statistically significant difference in lowest recorded S_p_O_2_:F_i_O_2_ (S:F) ratio on study day 3, at *P* < 0.05. The lowest S_p_O_2_ for the day will be identified and used to generate the S:F ratio (based on the F_i_O_2_ at time of lowest S_p_O_2_ value).

Secondary/exploratory outcomes will be evaluated to identify statistically significant differences (*P* < 0.05) in (1) Lowest recorded S:F value on study days 1–2 and 4–8, or until extubation (whichever comes first); (2) Lowest Sequential Organ Failure Assessment (SOFA) score on study days 1, 3, 5, and 8; and (3) Highest COVID Ordinal Outcomes Scale score on study days 1, 3, 8, 15, and 29. On study day 29, we will also assess (1) Oxygen-free days through day 28; (2) Ventilator-free days through day 28; (3) ICU-free days through day 28; and (4) Hospital-free days through day 28.

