#### Protocol modifications

Any modifications to the approved clinical protocol will be developed in consultation with the DSMB and will be implemented only after approved by the OSU IRB and FDA. Once the protocol change is approved by the IRB, the DSMB and NIAID will be notified.

The PI will then schedule an educational session to review changes in the protocol with the participation of each team member recorded.Sample size. Sample size calculations are based on differences in % carotid S_p_O_2_ between saline and CDP‐choline treatment groups in SARS CoV‐2-infected mice (unpublished data). Effect sizes post treatment were 1.32 in IAV and 1.4 in SARS CoV‐2 infected mice. With 24 subjects in the 2.5 and 5 mg/kg/dose treatment groups and 24 controls, and allowing 5% missing data at day 3 (80 participants total), there is 80% power (*α* = 0.05) to detect an effect size of 0.9 in S:F ratio between any individual arm and control (0.39 effect size overall), 32% below that in our preliminary data.

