### Statistical analysis

All analysis will be based on intention to treat guidelines and reporting will follow CONSORT guidelines [65]. Data will be analyzed using STAT software (SAS; Cary, NC). The primary clinical outcome (S:F ratio on day 3) will be analyzed using either analysis of variance or a non-parametric Kruskal–Wallis test if analysis of variance assumptions (normality, homoscedasticity) are violated. Follow-up contrasts comparing each dose to control will be performed at *α* = 0.05/3 if the global test of differences between groups is rejected. If subject dropout due to mortality or discharge is present prior to day 3, the survivor average causal effect will employ a potential outcomes approach to account for potential survival bias and estimate the average causal effect of the intervention on S:F ratio among participants who would survive regardless of their intervention status, e.g., the always-survivors [66, 67]. The recommended citicoline dose for Phase 3 trials will be the dose achieving the greatest statistically significant improvement in day 3 S:F ratios, with consideration of key secondary endpoints (SOFA scores, etc.). Standardized mean differences will assess balance on baseline covariates across treatment arms. Competing risks analysis will assess differences between groups for competing time-to-event outcomes (e.g., hospital mortality, time to recovery, time off ventilator, discharge) [68].

Differences in SOFA scores between groups will be evaluated using non-parametric tests. A multinomial ordinal proportional odds model will estimate the odds ratio between study groups for COVID Ordinal Outcomes Scale. For outcomes with repeated assessments, generalized mixed models will evaluate differences between groups with a subject-level random effect to account for repeated measures. The mixed model accounts for data that are missing at random, when including baseline covariates associated with missing status. To account for potential non-ignorable dropout (e.g., due to mortality), a joint modeling approach will incorporate a shared random effect to simultaneously model the time-to-event process and longitudinal process [69].

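### The primary efficacy outcome is worded as an undirected significant difference with no comparator, so a significant four-arm test meets it even when no dose is shown better than placebo

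*Protocol article*

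**What the plan says.** Two places define the primary efficacy outcome. The Outcomes section has "The primary clinical outcome is a statistically significant difference in lowest recorded" S:F ratio on study day 3, at P < 0.05. The Primary Outcome row of Table 1 (the registration dataset) opens in the same way: "A statistically significant difference in lowest recorded". Neither says which arms are compared or which direction counts.

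Statistical analysis gives the procedure. Day 3 S:F "will be analyzed using either analysis of variance or a non-parametric Kruskal–Wallis test", the latter if the ANOVA assumptions fail. Then: "Follow-up contrasts comparing each dose to control will be performed at" α = "0.05/3 if the global test of differences between groups is rejected". No dose-versus-dose contrast is planned. Direction enters in the next decision, where the dose recommended for Phase 3 is "the dose achieving the greatest statistically significant improvement in day 3 S:F ratios", with secondary endpoints also considered.

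The sample size paragraph (placed under Protocol modifications) says "there is 80% power" at α = 0.05 "to detect an effect size of 0.9 in S:F ratio between any individual arm and control (0.39 effect size overall"), with 80 participants and 5% missing at day 3.

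**The concern.** A primary outcome should be a measurement, with the success rule stated separately. Here the two are merged, and the merged statement is looser than the trial's aim of showing that citicoline improves outcomes relative to standard of care.

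The first test applied to the outcome is a four-group ANOVA or Kruskal–Wallis test. It rejects for any departure from equality: a dose better than placebo, a dose worse than placebo, or two doses on opposite sides of placebo with neither clearly different from it. All three satisfy the definition in Outcomes and Table 1. A report could then state, correctly by the letter of the plan, that the primary efficacy outcome was met when no dose had been shown to beat placebo.

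**Working it through.** **Inputs.** Four arms, 1:1:1:1, 80 in total (Study design and setting; Intervention description). With 5% missing at day 3, 80 × 0.95 = 76 evaluable, or 19 per arm. Effect 0.9 SD for one arm versus control, f = 0.39 overall, α = 0.05 (sample size paragraph). Contrasts at 0.05/3 = 0.0167 after a significant global test (Statistical analysis). The sample size paragraph also mentions 24 per group, which does not fit 80 at 1:1:1:1; 19 is used because it follows from 80 less 5% and reproduces the stated power.

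**Step 1: reproduce the plan's figure.** For arm means 0, 0, 0, 0.9 (SD = 1) the grand mean is 0.225. Then f = √[(3 × 0.225² + 0.675²)/4] = √0.1519 = 0.390, the stated overall effect size. The four-group F test at 0.05 with N = 76 has power 0.802. So the stated 80% is reproduced by the global test at 0.05. (An unadjusted two-sided comparison of two arms at 0.05 with 19 to 20 per arm gives nearly the same by the normal approximation, 0.79 to 0.81, so the match alone does not identify the test.)

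**Step 2: one contrast at 0.05/3.** Two-sided, 19 per arm: 0.9 × √(19/2) = 2.774; the critical value is 2.394; Φ(2.774 − 2.394) = Φ(0.380) = 0.648. The t test gives 0.606. The plan does not state sidedness; one-sided at 0.05/3 the figures are 0.741 and 0.712.

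**Step 3: the two-stage procedure.** Simulation of 40,000 trials per scenario: normal data, equal variances, 19 per arm, global F test at 0.05, then two-sided dose-placebo contrasts at 0.05/3. Entries are percentages of all trials.

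| True dose effects versus placebo (SD) | Global P < 0.05 (outcome met as worded) | Met, and a dose superior | Met, no dose superior | Met, no contrast significant either way |
|---|---|---|---|---|
| 0, 0, 0 | 4.9 | 1.5 | 3.4 | 2.0 |
| 0, 0, −0.9 | 80.3 | 1.6 | 78.7 | 17.6 |
| −0.45, 0, +0.45 | 60.8 | 14.8 | 45.9 | 31.4 |
| 0, 0, +0.9 | 80.0 | 61.2 | 18.8 | 17.5 |
| 0, +0.9, +0.9 | 90.9 | 77.5 | 13.4 | 12.8 |

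**Step 4: reading the table.** With one harmful dose, no dose is superior in 78.7/80.3 = 98% of the trials that meet the outcome. With doses on opposite sides of placebo, 31.4/60.8 = 52% of the trials that meet it have no significant dose-placebo contrast at all. In the scenario that the stated effect sizes describe, one dose at +0.9 SD, 18.8/80.0 = 23.5% of the trials that meet it show no dose to be superior.

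**The case against.** The strongest reply is that Statistical analysis already supplies what the outcome wording omits. It limits the contrasts to each dose against control, and it requires improvement for the recommended Phase 3 dose. Under that procedure a harmful dose cannot be recommended, and with all arms equal a benefit is claimed in only about 1.5% of trials. In the harmful-dose scenario the two-sided contrasts also do their job: they flag that dose as significantly worse in 61.4% of all trials, which is 61.4/80.3 = 76% of those with a significant global test. This stands. But the sentence on improvement governs which dose goes forward. It does not say when the primary outcome is met.

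A second reply is that the −0.9 and ±0.45 SD patterns are chosen for illustration and that any ANOVA lacks direction. That is also true, and those rows are not forecasts. The +0.9 SD row does not depend on them: it uses the plan's own effect size and still leaves about 19% of all trials with the outcome met and no dose shown superior.

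A reader might also infer that P < 0.05 in Outcomes and Table 1 contradicts the 0.05/3 in Statistical analysis. The documents do not support that. P < 0.05 fits the global test, whose power at that level is the stated 80%, and 0.05/3 applies to the three contrasts that follow a rejection. These are consecutive stages of one procedure. What can be said is narrower: Outcomes and Table 1 do not say which test their P < 0.05 refers to, and Statistical analysis does not restate the level of the global test.

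**Conclusion.** The point holds as a defect in the stated success rule. As worded, the primary efficacy outcome is met by any significant four-arm test, whatever its direction and whichever arms produce it. With 19 evaluable per arm, that happens in about 80% of trials when one dose lowers S:F by 0.9 SD. It also happens in 80% when one dose raises S:F by 0.9 SD, although superiority over placebo at 0.05/3 is then shown in only about 61%.

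The figures assume normal data with equal variances, ANOVA rather than Kruskal–Wallis, two-sided contrasts, and no loss to death or discharge before day 3 beyond the 5% allowed.

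Two stronger conclusions are not supported: that the plan could recommend a harmful dose, and that its significance levels contradict each other. The point should be corrected because it concerns what may be claimed as a positive primary result; the design and the test procedure can stay as they are.

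**What to change.** In Outcomes and in the Primary Outcome row of Table 1:

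- Define the primary efficacy endpoint as the lowest S:F ratio on study day 3.
- Define primary efficacy success as a significant global test at 0.05, followed by at least one citicoline dose with a higher S:F ratio than placebo on its contrast at 0.05/3, and state whether the contrasts are two-sided.
- State that P < 0.05 refers to the global test, and repeat that level in Statistical analysis.
- State that a significant global test alone is not a positive result, and that a significantly lower S:F ratio on a dose is not one either and will be reported as evidence of harm.

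In the sample size paragraph, give the probability of success under this rule next to the 80%: about 61% with one effective dose at 0.9 SD and 19 evaluable per arm.

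The cost is wording and a registry update. No test, level or sample size has to change. The trial will be called positive less often (about 61% rather than 80% with one dose at +0.9 SD), because the trials removed are almost all ones in which no dose was shown to be better than placebo.

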#### Participant timeline

The timing of study procedures is based on the time at which consent was obtained, which is defined as “Time 0”. Chest X-ray will be performed and baseline Sequential Organ Failure Assessment (SOFA) and COVID Ordinal Outcomes Scale (HRS) scores will be calculated at Time 0. Study test agents will be administered by study personnel while the patient is hospitalized, with the first dose being administered within 4 h of Time 0. If the patient is discharged prior to completion of the study medication, no further study medication will be administered.

Individual patient schedules are shown below and in Fig. 2.

**Fig. 2 Fig2:**
[figure not shown]
Individual patient schedule. Patients will receive test agent (citicoline or saline placebo) every 12 h for 5 days. Patients will be monitored out to day 29. ABGs—arterial blood gases; CBC/CHEM—complete blood count and chemistry panel; COOS—COVID Ordinal Outcomes Scale; CXR—chest X-ray; S:F—S_a_O_2_:F_i_O_2_ ratio; SOFA—Sequential Organ Failure Assessment

Day 0–1:Informed consent will be obtained.Order for study drug will be placed by the investigator.Initial clinical data will be obtained by research staff using the EMR and recorded in the REDCap study database. Missing laboratory data will be ordered by the investigator.Blood will be drawn from all patients prior to the first treatment dose for laboratory studies.Study drug will be administered i.v. by the bedside nurse operating within their usual scope of practice. The timing of study drug administration may be adjusted up to 4 h on subsequent dosing to achieve standard dosing times.Clinical information, including other drugs administered, will be recorded by the research team into the REDCap study database.

Days 1–5:The patient will be assessed daily by study team for evidence of adverse drug reactions.Dosing with the test agent will continue every 12 h until each subject has received 10 doses total.Laboratory samples will be collected according to the study timeline.Clinical information, including other drugs administered, will be recorded by the research team into the REDCap study database.

Days 6–8:The patient will be assessed daily by study team for evidence of adverse drug reactions or clinical change.Laboratory samples will be collected according to the study timeline.Clinical information, including other drugs administered, will be recorded by the research team into the REDCap study database.

Days 9–29:Patient will be assessed daily by study team for evidence of adverse drug reactions or clinical change.Patients discharged home prior to day 29 will be called on day 29 to verify vital status and discharge location.Patients who withdrew from the trial at any point prior to the cessation of test agent administration

#### Participant stopping rules and withdrawal criteria

Participants may be prematurely terminated from the study for the following reasons: (1) The participant elects to withdraw consent from all future study activities, including follow‐up; (2) The participant dies; (3) The Investigator no longer believes participation is in the best interest of the participant; or (4) The Investigator believes that an SAE in the patient may be attributable to the test agent.

Participants who withdraw or are withdrawn will not be replaced if they have received at least one dose of the investigational agent.

Patients wishing to withdrawal early from the study (i.e., before all 10 doses were administered) will be asked if they are agreeable to follow-up phone call on day #29. If approval is granted, they will be called on day 29 to verify vital status and discharge location. Patients opting complete withdrawal from the study will not be contacted further.

#### Protocol modifications

Any modifications to the approved clinical protocol will be developed in consultation with the DSMB and will be implemented only after approved by the OSU IRB and FDA. Once the protocol change is approved by the IRB, the DSMB and NIAID will be notified.

The PI will then schedule an educational session to review changes in the protocol with the participation of each team member recorded.Sample size. Sample size calculations are based on differences in % carotid S_p_O_2_ between saline and CDP‐choline treatment groups in SARS CoV‐2-infected mice (unpublished data). Effect sizes post treatment were 1.32 in IAV and 1.4 in SARS CoV‐2 infected mice. With 24 subjects in the 2.5 and 5 mg/kg/dose treatment groups and 24 controls, and allowing 5% missing data at day 3 (80 participants total), there is 80% power (*α* = 0.05) to detect an effect size of 0.9 in S:F ratio between any individual arm and control (0.39 effect size overall), 32% below that in our preliminary data.

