## Methods

### Participants, interventions, and outcomes

#### Study design and setting

SCARLET is a single-center, double‐blinded, placebo‐controlled, and randomized Phase 1/2 trial of i.v. citicoline in adult patients of any sex, gender, age, or ethnicity who are hospitalized with HARF following SARS CoV‐2 infection (Table 1). Patients will be enrolled at The Ohio State University (OSU) Wexner Medical Center (OSU WMC) and OSU WMC Hospital East (OSU East), both of which are in Columbus, Ohio, USA. The goals are to confirm citicoline safety over a range of doses and demonstrate potential for efficacy in this population for at least one citicoline dose. The trial will enroll 20 patients per dose for 3 citicoline doses (0.5, 2.5, and 5 mg/kg every 12 h for 5 days) along with 20 placebo‐treated controls (See Fig. 1).

**Table 1 Tab1:** WHO trial registration dataset

**Primary Registry and Trial Identifying Number**	Clinicaltrials.gov: NCT05881135
Date of Registration in Primary Registry	5/31/2023
Secondary Identifying Numbers	Federal Award Identification Number: U01AI677784 FDA IND: 162,806 OSU IRB protocol number: 2022H0451
Source of Monetary Support	NIAID Co-operative agreement
Primary Sponsor	[name] [name], MD
Secondary Sponsor(s)	None
Contact for Public Queries	[name] [name], MD Professor, Dept. of Internal Medicine, The Ohio State University [contact] [name]
Contact for Scientific Queries	Principal Investigators: [name] [name], MD Professor, Dept. of Internal Medicine, The Ohio State University [contact] [name] [name] [name], DVM, PhD, ATSF Professor, Dept. of Veterinary Biosciences, The Ohio State University [contact] [name] [name]
Public Title	Citicoline for hospitalized COVID patients
Scientific Title	SCARLET (Supplemental Citicoline Administration to Reduce Lung injury Efficacy Trial)
Countries of Recruitment	United States of America
Health Condition Studied	COVID-19
Intervention	Investigative agent: 0.5, 2.5, or 5 mg/kg) of Somazina® citicoline (CDP-choline) solution for injection (Ferrer Internacional, S.A., Barcelona, Spain) diluted in sterile USP-grade normal saline to 10 ml final volume, administered i.v. every 12 h for 5 days Placebo: 10 ml sterile USP-grade normal saline, administered i.v. every 12 h for 5 days

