### Interventions

#### Intervention description

Patients will be randomized 1:1:1:1 to receive one of 3 doses (0.5, 2.5, or 5 mg/kg) of Somazina® citicoline solution for injection (Ferrer Internacional, S.A., Barcelona, Spain) diluted in sterile normal saline or placebo (sterile normal saline). Somazina® is approved by the European Medicines Agency for use with a prescription in Europe. Patients will be treated with study agent every 12 h for up to 5 days.

Citicoline will be provided in sterile, single-use, Type I neutral glass ampoules containing 1000 mg active pharmaceutical ingredient (citicoline) dissolved in 4 ml water (final concentration 250 mg/ml), with HCl added to normalize pH; no other excipients are present. Study ampoules will be shipped from Ferrer directly to the IDS at OSU WMC and stored at room temperature in the dark. The immediate package of this investigational new drug will be labeled with the statement “Caution: New Drug – Limited by Federal (or United States) law to investigational use.”

Study drugs will be prepared on the day of use by a research pharmacist in the IDS at OSU WMC. Citicoline solution will be diluted in USP-compliant sterile normal saline to a final volume of 20 ml containing the appropriate total daily dose for each patient (1, 5, or 10 mg/kg/day, based on their ID number). Doses will be rounded to the nearest 0.1 ml per standard rounding rules. Two 10-ml aliquots will then be prepared in sterile disposable syringes labeled with the patient ID number for administration 12 h apart and then kept refrigerated. Unused undiluted or diluted citicoline will be discarded by the IDS pharmacist and documented as such. Placebo controls will receive 10 ml USP-compliant sterile normal saline every 12 h for 5 days.

Each 10 ml dose of test agent will be delivered by nursing staff as a slow i.v. bolus over 3–5 min and immediately documented in the EMR. EMRs will be reviewed daily by the clinical trial coordinator to ensure test agent administration has occurred and been documented.

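### The 80% power claimed for each dose against control is the power of the global four-arm test; a single dose-control contrast at 0.05/3 has about 61%

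*Protocol article*

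**What the plan says.** The sample size text sits at the end of the Protocol modifications section. It begins "With 24 subjects in the 2.5 and 5 mg/kg/dose treatment groups and 24 controls", continues "and allowing 5% missing data at day 3 (80 participants total", and claims 80% power at alpha 0.05 "to detect an effect size of 0.9 in S:F ratio between any individual arm and control (0.39 effect size overall". It describes 0.9 as 32% below the preliminary data, which are mouse effect sizes of 1.32 and 1.4. It gives no number for the 0.5 mg/kg arm.

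Elsewhere the design is consistent. Study design and setting says "The trial will enroll 20 patients per dose for 3 citicoline doses", plus 20 placebo controls. Table 1 has "Planned: 80 Enrolled: 15". Intervention description says "Patients will be randomized 1:1:1:1 to receive one of 3 doses" or placebo.

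Under Statistical analysis, day-3 S:F is first compared across all four groups by ANOVA, or by Kruskal–Wallis if the assumptions fail. Each dose is then compared with control at 0.05/3, "if the global test of differences between groups is rejected". The recommended Phase 3 dose is the one with the greatest statistically significant improvement in day-3 S:F, with key secondary endpoints also considered.

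**The concern.** Two things do not fit. First, the power is stated for a single dose against control at alpha 0.05, but the analysis makes that comparison at 0.05/3 and behind a global test. Power at 0.05 is not the power of the planned contrast.

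Second, the group sizes conflict. Three groups of 24 make 72, which leaves 8 of 80 for the fourth arm, and four groups of 24 would make 96. Neither is 20 per arm at 1:1:1:1, and the 5% missing-data allowance does not bridge the gap.

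The contrasts are what identify a dose for Phase 3. If their power is overstated, a dose that fails its contrast may be read as better excluded than it is, and the margin against the animal data looks wider than it is.

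**Working it through.** **Inputs.** 80 planned, 20 per arm, 1:1:1:1 (Study design and setting, Table 1, Intervention description). 5% missing at day 3, d = 0.9, overall effect size 0.39, alpha 0.05 (sample size text). Contrast level 0.05/3 = 0.0167 (Statistical analysis). Evaluable: 80 × 0.95 = 76, or 19 per arm. Sidedness is not stated; two-sided is assumed. The 0.39 is read as Cohen's f.

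**Step 1: reproduce the plan's 80%.** With one arm 0.9 SD away from three equal arms, f = 0.9 × √3 / 4 = 0.390, which matches the stated overall effect size. The noncentrality is N f² = 76 × 0.39² = 11.56. Against the F(3, 72) critical value of 2.73 at alpha 0.05, power is **80.2%**. With all 80 evaluable it is 82.5%. So the figure reproduces as global-test power for the design of 20 per arm.

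**Step 2: power of one dose-control contrast.** The noncentrality is d / √(2/n). For n = 19 it is 0.9 / √(2/19) = 2.774. The two-sided critical value at 0.05/3 is 2.511 on 36 df (two-sample t), or 2.451 on 72 df (ANOVA pooled error). Power for d = 0.9:

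| n per arm | alpha | two-sample t | pooled error |
|---|---|---|---|
| 24 | 0.05 | 86.3% | 87.0% |
| 23 | 0.05 | 84.7% | 85.5% |
| 20 | 0.05 | 79.2% | 80.2% |
| 19 | 0.05 | 77.0% | 78.1% |
| 24 | 0.05/3 | 73.4% | 75.0% |
| 23 | 0.05/3 | 71.2% | 72.8% |
| 20 | 0.05/3 | 63.5% | 65.5% |
| **19** | **0.05/3** | **60.6%** | **62.7%** |

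The stated 24 per group at the stated 0.05 gives about 86%, not 80%. No row at 0.05/3 reaches 80%.

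**Step 3: add the global gate.** In simulation with 19 per arm, requiring the global F test to reject as well, power per contrast is 61–62% (pooled error) or 59–60% (two-sample t) when one, two or three doses differ from control by 0.9 SD.

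**Step 4: detectable effect.** Solving for 80% power at n = 19 and 0.05/3 gives d = 1.09 (two-sample t) or 1.07 (pooled error). The plan's margin is (1.32 − 0.9)/1.32 = 32%. The margin for a contrast is (1.32 − 1.09)/1.32 = 17% to (1.32 − 1.07)/1.32 = 19%.

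**Step 5: trial level.** The chance that at least one truly effective dose is declared, with the gate and 19 per arm, is about 61% if one dose has a 0.9 SD effect, about 77% if two do, and 79–80% if all three do (pooled error; 59%, 76% and 79% with two-sample t).

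**Step 6: group sizes.** 3 × 24 = 72; 80 − 72 = 8; 4 × 24 = 96. 24 × 0.95 = 22.8, and 20 / 0.95 = 21.1. None of these gives 20 per arm.

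**The case against.** The strongest defence is that the sample size is not miscalculated. The global test comes first in the planned sequence, the contrasts are called follow-up, and the text does disclose the overall effect size, the alpha and the total. On those inputs 80% is right. That stands, and it limits the fault to the comparison to which the figure is attached.

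A reader might infer that the 24s are what produce the 80%. They are not: 24 per group at 0.05 would give about 86%. The stray number does not inflate the claim, and changing 24 to 20 would leave the power statement wrong. Where the 24 came from cannot be established from the document.

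The global test is also not the only route to about 80%. A single comparison with 20 per arm, nobody missing and alpha 0.05 gives 79.2%. Some variants with 23 or 24 per arm and another alpha come close too, for example 80.1% with 23 per arm at one-sided 0.05/3. The global reading is preferred because it uses the stated total, missing-data allowance and alpha, and also yields the 0.39. None of the alternatives rescues the claim for the two-sided contrast at 0.05/3.

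Finally, this is a Phase 1/2 study with safety among its primary goals, seeking preliminary evidence of benefit at one or more doses, and dose choice also weighs secondary endpoints. That limits the consequences, but it does not make the stated power correct for the comparison it names.

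**Conclusion.** The point holds as a misattribution. The 80% belongs to the global ANOVA (f = 0.39, 76 evaluable), and the plan assigns it to each dose against control. For that comparison as planned, power at 0.9 SD is about 61%, so a single contrast misses such an effect about 39% of the time rather than 20%. The effect detectable with 80% power is about 1.1 SD. The conflict between 24 and 20 per arm is a separate inconsistency that does not drive the 80%.

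It would go too far to say that the trial as a whole misses a 0.9 SD benefit 39% of the time. That is the single-contrast figure, and it is the trial-level figure only if just one dose works; with two or three effective doses the chance of declaring at least one is about 77–80%. Nor do the documents show that 80 patients is the wrong number for the global test.

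Assumptions: two-sided tests, normal data with equal variance, 5% missing spread evenly, no covariate adjustment. A normal approximation gives 64.8% in place of 60.6%; a rank-based contrast would have somewhat lower power, about 58%.

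**What to change.** Rewrite the sample size text as follows:

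- State 20 randomized per arm (80 in total, 1:1:1:1), with about 19 evaluable per arm after 5% missing data, and delete the 24s.
- Label the 80% as the power of the global four-arm ANOVA at alpha 0.05 and f = 0.39 (one arm 0.9 SD from the other three).
- Report about 61% power for 0.9 SD in one dose-control contrast at 0.05/3, and 80% only for about 1.1 SD.
- Replace the 32% margin for the contrasts with 17–19% below the 1.32 mouse effect.
- Note that 61% is per contrast, and that the chance of declaring at least one effective dose rises to about 77–80% if two or three doses each have a 0.9 SD effect.

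The cost is wording only. Enrolment, randomization and the analysis are unchanged; the stated power becomes less favourable.
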